## Outcomes

The **primary outcome** of this study is preparation for decision-making, measured using the Preparation for Decision Making (PrepDM) scale. PrepDM has 10-items that address concepts of preparedness for decision-making. It has successfully discriminated between different educational resources in randomised trials and is valid and reliable.

### Secondary outcomes

- Management intentions

We adapted items from Hersch et al. for decisions about care for low back pain:

- At the moment, which of the following best describes your intentions about **having a scan (x-ray, CT, MRI)** for your low back pain?

*Response options:*

- I definitely will have a scan
- I am likely to have a scan
- I am unsure

---

 Hersch J, et al. BMJ Open. 2014 May 15;4(5):e004990.

- I am NOT likely to have a scan
- I definitely will NOT have a scan
  
- At the moment, which of the following best describes your intentions about **taking opioids (strong prescription pain medicines e.g. oxycodone, codeine, tramadol)** for your low back pain?
  - I definitely will take opioids
  - I am likely to take opioids
  - I am unsure
  - I am NOT likely to take opioids
  - I definitely will NOT take opioids
  
- At the moment, which of the following best describes your intentions about **using heat (e.g. heat packs, hot water bottle)** for your low back pain?
  - I definitely will use heat
  - I am likely to use heat
  - I am unsure
  - I am NOT likely to use heat
  - I definitely will NOT use heat
  
- At the moment, which of the following best describes your intentions about **seeking physical therapy on your back (e.g. massage or spinal manipulation)**?
  - I definitely will seek physical therapy
  - I am likely to seek physical therapy
  - I am unsure
  - I am NOT likely to seek physical therapy
  - I definitely will NOT seek physical therapy
  
- At the moment, which of the following best describes your intentions about **staying active** while you have low back pain?
  - I definitely will stay active
  - I am likely to stay active
  - I am unsure
  - I am NOT likely to stay active
  - I definitely will NOT stay active

Participants who report being definitely/likely to seek imaging or opioids for their low back pain will be classified as having “intentions for medical care”.

- Reassurance

- How reassured are you that there is no serious condition causing your low back pain? (from Traeger et al) 0 - not reassured at all; 10 - completely reassured
- Acceptability
  - Did you read the fact sheet all the way through?
    - If Yes - how many minutes did you spend reading the fact sheet?  
[ \_\_\_\_\_ min] .
    - If No - How much of the fact sheet did you read?  
[options: most / some / a little]
  - How would you rate the length of the fact sheet?  
[options: much too short / a little too short / just about right / a little too long / much too long]
  - How much of the information in the fact sheet was new to you?  
[options: all / most / some / none]
- The fact sheet talked about different ways to manage back pain. It mentioned **medical care (pain medicines, imaging, surgery)** and **non-medical care (massage, heat, staying active)** for back pain. Did you feel the fact sheet was: [options: leaning very much towards medical care/ leaning a bit towards medical care/Balanced/ Leaning a bit towards non-medical care/Leaning very much towards non-medical care]
- How strongly do you agree or disagree with each of the following statements.  
[options: strongly agree / agree / neither agree nor disagree / disagree / strongly disagree]
  - I found the information in the fact sheet clear and easy to understand.
  - I would recommend this fact sheet to other people who are considering their options to treat low back pain.
- Fidelity
  - How did you receive the fact sheet
    - From my GP
    - Via SMS from my GP practice
    - Social media
    - Other [please describe]
- Implementation

---

 Traeger AC et al. JAMA Neurol. 2019 Feb 1;76(2):161-169.

- We will also conduct semi-structured interviews and or focus groups (depending on feasibility) with up to 20 clinicians and 20 patients (interview only) to identify barriers and facilitators to implementation of the fact sheets in primary care. We used the COM-B framework to create our initial interview guide (Appendix D) which will be updated iteratively as interviews/focus groups progress. For the clinician focus groups if feasible, we will conduct up to 3 focus groups with 5-6 GPs in each group.
- Recruitment rates
  - Proportion of people exposed to the survey advertisement who consent to participate

**Nested study:**

**BACKGROUND:** High-quality primary care-based research requires adequate response rates. A recent systematic review identified some promising strategies including monetary incentives. However, most evaluations to date have focused on mail and telephone-based patient experience surveys.

**AIM:** assess the effect of different survey advertising methods using fact sheets embedded in consultation software (BetterConsult provided by the company HealthShare), on recruitment rate.

**DESIGN:** ABACAD replicated time series design where “A” are control periods and “B” and “C” are different behaviourally informed advertising strategies.

**PARTICIPANTS:** Patients who have recently seen their GP for back pain and have received back pain fact sheet. Participants could receive a fact sheet via one of two methods. The first method is directly from their GP who prints and/or emails the sheet to their patient. The GP determines which sheet they will provide and so receipt of the JAMA or ACHSQ fact sheet is non-random. The second method is patient-led access to a back pain fact sheet via an SMS system called BetterConsult. BetterConsult invites a patient to receive a back pain fact sheet after they see their GP. Whether the patient receives the JAMA or ACHSQ fact sheet is determined randomly by the fact sheet distributor, HealthShare. Patients can view the sheet on their smartphone or print the sheet out and their GP will be notified. GPs can open and discuss the fact sheet with their patient during the consult if they wish. Twenty-four hours after their consultation with the GP, HealthShare sends patients an SMS containing a link to the fact sheet. Final sample size will be determined by monthly reach of study advertising.

**EXPOSURES:** Control Period A – Advertisement is a clickable link and QR code with the words “Have your say about this fact sheet” in a red box in the top right corner of the fact sheet. Intervention Period B – Advertisement is a clickable link that mentions a financial incentive to participate: “Have your say about this fact

 Price et al (2022) Med Care. 2022 Dec; 60(12): 910–918.

sheet. Complete a short survey **for your chance to win**” is written in a red box in the top right corner of the fact sheet. Intervention Period C – Advertisement is a clickable link with phrasing that appeals to social good: **“Help us improve fact sheets for people with back pain.”** Intervention Period D – Advertisement is a clickable link with phrasing that appeals to both social good and provides financial incentive: **“Help us improve fact sheets for people with back pain. Complete a short survey for your chance to win”** in a red box in the top right corner of the fact sheet.

COPYRIGHTED MATERIAL REDACTED

COPYRIGHTED MATERIAL REDACTED

Intervention period B

COPYRIGHTED MATERIAL REDACTED

COPYRIGHTED MATERIAL REDACTED

**Figure 4:** Three different advertising strategies to increase response rate to a fact sheet-based survey.

**OUTCOMES:** Proportion of people exposed to the survey advertisement who consent to participate

**SAMPLE SIZE:** A previous study comparing recruitment rates of different online recruitment methods suggest 27% response rate. To detect a difference in response rate of 5% (27% in control group, 32% in intervention group), with 80% power and 0.05 alpha, sample size required would be 1306 participants in each group (total n= 5224). The recruitment will stop at 5224 participants.

**ANALYSIS:** Descriptive analyses will be done to report the response rate for all participants according to trial period. We will compare the number and proportion of participants responding to messages.

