The nature of the first two access methods means that we can make a randomised comparison of the survey responses to the two fact sheets delivered via patient-led access, but not those delivered by the GP-led access, ie in the consult by print or email. For people accessing the fact sheet via the third method (social media), the exposures will be randomised using Qualtrics software hosted by The University of Sydney. Data from patients receiving a fact sheet using the three methods (GP-led access vs Patient-led access vs Social Media) will be analysed separately in a sensitivity analysis.

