| Update                                                                                             | 
This study is quasi randomised. Participants are allocated to intervention and control groups via three methods. The first method is based on GP discretion as to which study fact sheet they provide to their patient. The comparison of outcomes for people allocated to fact sheet interventions via this method is therefore non-random. The second allocation method is random. Based on a computerised random number list, a GP software provider will allocate access to either the intervention or control fact sheet, for one month at a time for the duration of the trial. The comparison of outcomes for people allocated to interventions via this method is therefore based on a randomised computer generated sequence.
 
The third allocation method will be random. Participants via social media advertisement will be allocated to either intervention or control fact sheet randomly.
                                                                                                                                                                                                                                                                                                                                                                                         |

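### In the SMS stream the monthly fact-sheet list and the ABACAD advertising periods are not balanced against each other, so message contrasts can pick up sheet differences

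*Supplement*

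**What the plan says.** **Sheet allocation.** The protocol (Design, participants, and setting; Nested study) says that in the patient-led stream the distributor determines the sheet at random, and gives no unit of allocation. The registry record (Study design, sequence generation, as updated) gives the unit: "Based on a computerised random number list", access is set to one sheet or the other "for one month at a time for the duration of the trial".

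**Message allocation.** The Nested study section describes an "ABACAD replicated time series design". A is the control wording, B an incentive, C an appeal to social good, and D both. The wording sits in a box on the fact sheet. Period length and number of cycles are not given. The nearest hint, "Final sample size will be determined by monthly reach of study advertising", concerns sample size, not period length.

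**Other streams.** For GP-led access, "The GP determines which sheet they will provide and so receipt of the JAMA or ACHSQ fact sheet is non-random". For social media, "the exposures will be randomised using Qualtrics software hosted by The University of Sydney". The nested study covers the GP-led and patient-led streams only.

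**Analyses.** The nested analysis is descriptive and reports response by trial period, with no breakdown by sheet. The primary analysis compares PrepDM between sheets with no term for message. The protocol separates the three access methods only in a sensitivity analysis.

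**The concern.** The nested study sets out to "assess the effect of different survey advertising methods using fact sheets embedded in consultation software". In the SMS stream, a person sent the link in a given month receives one sheet and one message, both fixed by the date. There are few months and few periods, so a list drawn without regard to the messages will usually show some messages more under one sheet than the other. Any difference between the sheets in how readily people respond then enters the message comparison.

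The reverse route concerns the main trial. PrepDM is measured only in people who choose to answer the survey. If an incentive or an appeal changes who answers, and the sheets are shown with different mixes of messages, the JAMA and ACHSQ respondents in this stream may differ before any effect of the sheet.

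**Working it through.** **Inputs.** Sheet unit of one month (registry record). Message order ABACAD (Nested study). Recruitment of up to 12 months (Recruitment section). Nested target of 27% versus 32%, 80% power, alpha 0.05. Assumptions: one-month message periods, because no length is given; two-sided tests; and a difference in response between sheets of 1 to 5 percentage points, because the documents give none.

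**The plan's own figures.** Two proportions, pooled variance, no continuity correction:

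n = [1.960·√(2·0.295·0.705) + 0.842·√(0.27·0.73 + 0.32·0.68)]² / 0.05² ≈ 1305 per group. The plan states 1306, and 4 × 1306 = 5224. For the main trial, a difference of 6, SD 26 and 90% power give 395 per arm, or 790. Both stated sizes reproduce; the issue is the schedule, not the sample size.

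**Do B, C and D each meet both sheets in the SMS stream?**
- One cycle (6 months): B, C and D have one month each, so each meets exactly one sheet.
- Two cycles (12 months), independent monthly draws: each of B, C and D has two months, which differ in sheet with probability 1/2. All three: (1/2)³ = 12.5%.
- Two cycles, list forced to 6 months per sheet: 2³·C(6,3)/C(12,6) = 160/924 = 17.3%.

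**Average imbalance against control A.** This is the mean absolute difference between the share of a message's months spent on one sheet and the same share for A, with independent draws.
- One cycle: a message's share is 0 or 1, and A's share has mean 0.5, so the mean difference is 0.50.
- Two cycles: with probability 1/2 the message has one sheet only (mean difference 0.5); otherwise its share is 0.5, and the mean distance of A's share from 0.5 over six months is 0.9375/6 = 0.156. Result: 0.5·0.5 + 0.5·0.156 = 0.33.

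**Distortion of a message contrast in the SMS stream** = imbalance × sheet difference in response.

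| Schedule | Imbalance | Sheets differ by 1 point | Sheets differ by 5 points |
|---|---|---|---|
| One cycle | 0.50 | 0.5 | 2.5 |
| Two cycles | 0.33 | 0.3 | 1.6 |

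The target difference is 5 points, so the upper end is half of it.

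**Incentive exposure by sheet.** Over all independent 12-month sequences for two cycles, the share of months carrying an incentive (B or D) differs between the sheets in 84%, by 0.24 on average. With a forced 6:6 list it differs in 55%, by 0.20 on average.

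**The case against.** A reader might infer that sheet and message are confounded throughout both studies. The documents do not support that, for these reasons:

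- **Period length is unknown.** All the probabilities above assume one-month periods. Shorter periods or more cycles would weaken the overlap. This stands; it makes the size conditional but does not remove the missing link between the schedules.
- **Only the registry record states the monthly unit.** The protocol's own wording would also fit randomisation per patient. If that is what the distributor does, the problem disappears, and the protocol should say so.
- **Certain aliasing of B, C and D holds only for a single cycle of one-month periods.** The design is called replicated. With two cycles, any one message has a 50% chance of meeting both sheets under independent draws.
- **Sheet and message are not inseparable.** A recurs three times per cycle. In one cycle A falls under both sheets with probability 1 − 2·(1/2)³ = 75%, and an additive separation is then possible. What one cycle loses is the message-by-sheet interaction, which the nested study does not aim to estimate. However, no such separation is planned.
- **Other streams are not tied to the list.** GPs choose the sheet in one stream and Qualtrics randomises it in the other. The planned analysis by access method would give a social media estimate free of this problem.
- **Harm to PrepDM is not shown.** It requires messages to change who responds in a way related to PrepDM, which the documents do not quantify. The misalignment also arises by chance and has no predictable direction.

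**Conclusion.** The point holds for the patient-led stream. As written, the plan sets sheet and message by separate calendar schedules, does not cross them, and ignores each in the analysis of the other.

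With one-month periods, full crossing of B, C and D with both sheets is impossible in one cycle and unlikely (12.5% to 17.3%) in two. The resulting average distortion of a message contrast in this stream is about 0.3 to 2.5 points. That rests on independent monthly draws and an assumed sheet difference in response of 1 to 5 points.

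For PrepDM, the SMS-stream comparison could be affected, by an amount that cannot be given from the documents. The pooled main comparison is diluted by the other two streams, and it would go too far to call it confounded as a whole. This is a worthwhile and inexpensive improvement; it does not invalidate the trial.

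**What to change.** 1. State the message period length, the number of cycles and the unit of sheet allocation in the protocol, and reconcile this with the registry record.
2. For the remaining months, constrain the distributor's list so that each of B, C and D, and A overall, runs under both sheets. With two cycles of one-month periods, this means each of B, C and D once under each sheet and the six A months split 3:3, in random order. If only one such cycle is possible, whole-month sheet blocks cannot achieve this, and the sheet would have to change within periods.
3. Alternatively, randomise the sheet per SMS if the distributor's system allows.
4. In the SMS stream, report and compare response rates by message stratified by sheet. For periods already run in which a message met only one sheet, compare it with A months under that same sheet.
5. Include message period as a stratum in the SMS-stream PrepDM comparison.

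The cost is a constraint on the distributor's random list and one extra stratification factor in each analysis, with no extra participants. The documents do not say what the distributor's system can do, so feasibility of items 2 and 3 must be confirmed. Items 4 and 5 do not depend on it.

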**Update**

JAMA Patient Page on low back pain. 1 page fact sheet delivered by GP or by SMS from GP practice. Content focuses on listing evidence-based treatment options. Freely available resource accessible at: <https://jamanetwork.com/journals/jama/fullarticle/2782184>

Participants can read the fact sheet at their own time and pace. GPs can open and discuss the fact sheet with their patient during the consult if they wish. Twenty-four hours after their consultation with the GP, HealthShare sends patients an SMS containing a link to the fact sheet on behalf of the GP. To monitor adherence participants will complete a study-specific questionnaire.

Participants can also access the fact sheet via an advertisement on social media (Facebook, Twitter, and Instagram). The advertisement will invite people who have recently seen their GP for back pain to view a fact sheet and complete a short survey.

Exposure: We are adding nested study within the original study to understand recruitment rates using ABACAD replicated time series design. Control Period A – Advertisement is a clickable link and QR code with the words "Have your say about this fact sheet" in a red box in the top right corner of the fact sheet. Intervention Period B – Advertisement is a clickable link that mentions a financial incentive to participate: "Have your say about this fact sheet. Complete a short survey for your chance to win" is written in a red box in the top right corner of the fact sheet. Intervention Period C – Advertisement is a clickable link with phrasing that appeals to social good: "Help us improve fact sheets for people with back pain." Intervention Period D – Advertisement is a clickable link with phrasing that appeals to both social good and provides financial incentive: "Help us improve fact sheets for people with back pain. Complete a short survey for your chance to win" in a red box in the top right corner of the fact sheet.

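### Nested study: the short-survey request appears only in advertisements B and D, so a difference from A should not be credited to the prize draw alone

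*Supplement*

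**What the plan says.** The four texts are in the Supplement, Nested study, under Exposures, and are repeated in the registry record's updated description of the intervention.

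- **A (control):** "Advertisement is a clickable link and QR code with the words “Have your say about this fact sheet".
- **B:** introduced with "Advertisement is a clickable link that mentions a financial incentive to participate". The full text, as the registry record gives it, is "Have your say about this fact sheet. Complete a short survey for your chance to win".
- **C:** introduced with "Advertisement is a clickable link with phrasing that appeals to social good". The text is "Help us improve fact sheets for people with back pain".
- **D:** described as joining the social-good appeal to the financial incentive. The text is "Help us improve fact sheets for people with back pain. Complete a short survey for your chance to win".

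The aim is to "assess the effect of different survey advertising methods using fact sheets embedded in consultation software" on recruitment rate. The design is given as "ABACAD replicated time series design where “A” are control periods and “B” and “C” are different behaviourally informed advertising strategies"; D is defined only under Exposures. A is the sole named control. The outcome is the proportion of people exposed to the advertisement who consent. The analysis is descriptive: response rates by trial period, and a comparison of numbers and proportions responding to the messages.

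**The concern.** The protocol names its advertisements by mechanism: B is the incentive message, C the social-good message, D both. The main Background lists reimbursement incentives and appeals to social goods as the recruitment strategies of interest, and the nested study's own background singles out monetary incentives as promising. In B only the prize phrase is in bold, which suggests it is the intended active element. A reader of the results will naturally take B against A as what a prize draw does to recruitment.

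The texts do not isolate that. B and D carry an instruction to act and a cue that the task is a short survey, and A and C carry neither. A low-burden request might raise response without any prize, or learning that the task is a survey might lower it. A later study could then pay for prizes when free wording did the work, or drop them because the wording masked their effect. The comparison of C with B or D has the same weakness: a social-good appeal could look weaker or stronger than an incentive because only one of the messages mentions a short survey.

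**Working it through.** **1. The plan's own figure.** Inputs from Nested study, Sample size: 27% in control, 32% in intervention, 80% power, alpha 0.05 (two-sided assumed, as sidedness is not stated). With the pooled-variance formula, no continuity correction and a mean proportion of 0.295:

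n = [1.960 × √(2 × 0.295 × 0.705) + 0.842 × √(0.27 × 0.73 + 0.32 × 0.68)]² / 0.05² = 1305 per group.

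The plan states 1306, or 5224 over four groups. Power at 1306 per group is 80.0%. The figure reproduces and nothing here challenges it.

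**2. The four texts by component.**

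| Period | Opening line | Short-survey request | Prize phrase |
|---|---|---|---|
| A | invitation to comment | no | no |
| B | as A | yes | yes |
| C | social-good appeal | no | no |
| D | as C | yes | yes |

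The last two columns are identical: the request and the prize always appear or are absent together.

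**3. What each comparison measures.** Write G for the effect of the social-good opening in place of A's, S for the short-survey request and P for the prize phrase. Taking them as additive for illustration:

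- B − A = S + P
- C − A = G
- D − A = G + S + P
- B − C = S + P − G
- D − C = S + P (no such contrast is planned)

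S and P enter only as a sum, so no comparison of these four messages yields P alone. A larger sample would not change that. C − A is not affected.

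**4. With the request in all four texts.** S then cancels everywhere: B − A = P, C − A = G, D − A = G + P, B − C = P − G. In wording, the messages become a two-by-two of opening line and prize.

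**5. Size.** The documents give no value or sign for S. The planned difference is 32% − 27% = 5 points, so each point of S, in either direction, equals 1/5 = 20% of it. That sets a scale and is not an estimate.

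This check covers wording only. The text mentions a QR code for A alone, and the figure showing the advertisements is redacted, so I draw nothing from that.

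**The case against.** The strongest reply is that the stated question concerns whole messages. The aim speaks of advertising methods, the design of strategies, and the analysis of responses to messages. For that question B against A is a sound comparison as far as the wording goes, and the extra sentence is part of the strategy under test. This stands. The plan also nowhere commits itself to reporting B against A as a pure incentive effect; the labels describe content. That stands too, although labels by mechanism invite the narrower reading.

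A prize offer must state its condition, and the Monetary incentives section links entry in the draw to the completed instrument. Some mention of the survey is therefore inherent in an incentive message. This is partly right, but all four advertisements recruit to the same survey, so the same request fits A and C equally well.

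The outcome is consent, and everyone who follows the link reaches an invitation page summarising the study first. The wording gap therefore acts mainly on whether people click. It does not drop out, because the denominator is everyone exposed to the advertisement.

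A reader might infer that C is the comparator for D, so that the plan contains two confounded incentive contrasts. The documents do not support this: only A is a named control, C is an intervention period, and no D against C contrast is specified.

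**Conclusion.** The point holds as a limit on interpretation. In wording, B differs from A by a short-survey call to action and a prize draw together, and the descriptive analysis cannot separate them. The same applies to any ranking of C against B or D. The whole-message comparison remains valid for the stated aim, but a difference should not be credited to the financial incentive alone.

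It would go too far to say that the nested study cannot attribute any difference to the incentive, or that its comparison of messages is biased. The prize is part of what differs, and the package effect is unaffected by this wording point. The size and direction of the wording effect are unknown from the documents, so no amount of distortion can be claimed. The sample size and the PrepDM comparison are untouched. This is a cheap improvement to a secondary study.

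**What to change.** **If the nested periods have not started:** add the same neutral sentence, *Complete a short survey*, to A and C. In wording, B then differs from A, and D from C, only by the closing prize phrase.

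**If any period has already run with the present text:** keep the A wording constant across all control periods, describe B and D in the report as a short-survey call to action plus prize draw, and draw no conclusion on incentives alone. The documents do not say whether a nested period has run, so this should be settled first.

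**Cost:** an edit to two advertisements and a minor ethics and registry update. The real downside concerns timing. A is the repeated control in the ABACAD sequence, and A periods with old and new wording cannot be pooled as one control. Rewording partway would split the baseline, which is why the second route leaves A alone. Relabelling needs only a change of description.

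### The nested study's 80% power and 0.05 alpha assume independent individuals, but messages are assigned to whole periods, so both figures hold only if response does not vary between periods

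*Supplement*

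**What the plan says.** The nested study in the protocol is described as "ABACAD replicated time series design where “A” are control periods and “B” and “C” are different behaviourally informed advertising strategies". The Exposures paragraph adds a fourth wording, D, and defines every wording as belonging to a control or intervention period. The outcome is the share of people exposed to the advertisement who consent.

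The Sample Size paragraph takes "27% in control group, 32% in intervention group" and concludes that "with 80% power and 0.05 alpha, sample size required would be 1306 participants in each group (total n= 5224". The total is 4 × 1306, and recruitment is to stop there.

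The Analysis paragraph has two sentences. The first plans a descriptive report of response rates for each trial period. The second reads "We will compare the number and proportion of participants responding to messages". The updated statistical methods field of the registration record repeats both and adds nothing on periods. Neither place gives a between-period variance, an intraclass correlation, a period length or a number of passes through the sequence.

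**The concern.** The unit that receives a message is a period, not a person. Everyone shown a fact sheet in that period sees the same advertisement. In one pass of the printed sequence, A occupies three periods and B, C and D one each. If the underlying response rate moves from period to period for any reason (season, mix of practices, distributor activity), that movement is part of the error of a message-versus-control difference. Exposing more people within the same periods does not reduce it. A steady trend is not needed for this to happen.

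The sample size formula leaves this component out. At stake is whether 5224 exposures deliver the stated 80% power. Also at stake is whether a test or interval computed from counts pooled by message would have its nominal error rate.

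**Working it through.** **Inputs from the protocol (nested study, Sample Size and Design).** Control 27%, intervention 32%, power 80%, alpha 0.05, 1306 per group, sequence ABACAD.

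**Assumed, because the documents do not give them.** Between-period SD of the true response rate, τ, of 1 or 2 percentage points; number of passes m of 1, 2 or 4.

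**1. The plan's own figure.** Two-sided, pooled variance, no continuity correction:

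n = [1.96·√(2·0.295·0.705) + 0.8416·√(0.27·0.73 + 0.32·0.68)]² / 0.05² = 1304.7, so 1305 per group.

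The unpooled form gives 1302 and a one-sided test 1028. Power at 1306 per group is 80.0%. The printed 1306 is therefore the two-sided formula for independent individuals, with a design effect of 1.

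**2. Variance when messages are assigned by period.** With 3m control periods and m periods of a given message,

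Var(difference) = p_A(1−p_A)/1306 + p_B(1−p_B)/1306 + τ²·(1/(3m) + 1/m).

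The last term equals 4τ²/(3m) and does not contain the number of people.

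**3. Type I error of a two-proportion test on pooled counts (27% in both groups).** The SE used by the test is √(2·0.1971/1306) = 0.01737. For m = 1 the true SE is:
- τ = 0.01: √(0.000302 + 0.000133) = 0.02086, so the error rate is 2Φ(−1.96·0.01737/0.02086) = 2Φ(−1.632) = 0.103.
- τ = 0.02: √(0.000302 + 0.000533) = 0.02890, so 2Φ(−1.178) = 0.239.

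Simulation with 200,000 runs gave 0.103 and 0.237.

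**4. Power at a true 5% level, variance treated as known (27% vs 32%).** The binomial part is 0.4147/1306 = 0.0003175. For m = 1:
- τ = 0.01: SE = 0.02123, and Φ(0.05/0.02123 − 1.96) = Φ(0.395) = 0.65.
- τ = 0.02: SE = 0.02917, and Φ(1.714 − 1.96) = Φ(−0.246) = 0.40.

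| Passes | Type I error, SD 1 point | Type I error, SD 2 points | Power, SD 1 point | Power, SD 2 points |
|---|---|---|---|---|
| 1 | 10.3% | 23.9% | 65% | 40% |
| 2 | 7.6% | 15.3% | 72% | 54% |
| 4 | 6.3% | 10.3% | 76% | 65% |

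With τ = 0 every row returns 5% and 80%. Splitting one pass into six equal periods (about 2612 control and 871 message exposures) gives the same one-pass error rates and, to the nearest percent, the same power.

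**5. Variance estimated rather than known.** In one pass only the three A periods replicate a condition, which leaves 2 degrees of freedom and a critical t of 4.30. A rough noncentral-t calculation with noncentrality 0.05/0.02123 = 2.355 and 0.05/0.02917 = 1.714 gives power of about 28% and 18%.

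**6. Limit with unlimited exposures.** For one pass and τ = 0.02, power with known variance cannot exceed Φ(0.05/(0.02·√(4/3)) − 1.96) = Φ(0.205) = 58%.

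**The case against.** The strongest reply is that the nested study plans no test. Its analysis is called descriptive, no p-value, interval or decision rule is named, and alpha and power appear only in the sample-size sentence. The 95% intervals elsewhere in the protocol belong to other secondary outcomes. Rates are to be shown by period, so scatter among the control periods would be visible. All of this stands. A reader might infer that the study is set to declare a message effective with a 24% false-positive rate. The documents do not support that, because the pooled test whose error is computed above is not one they commit to.

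A reader might also take one pass as the plan. The design is an "ABACAD replicated time series design", and "replicated" could mean that the whole sequence repeats or only that A recurs. The documents do not settle it, so the result is shown for one, two and four passes. Repetition reduces the problem without removing it.

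Nor do the documents support much larger losses. Intraclass correlations of 0.01 or 0.05 would imply between-period SDs of about 4.4 or 9.9 points around 27%, and nothing in the text anchors such values.

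Finally, this is a secondary recruitment question, and the main preparation-for-decision-making comparison is not affected by it. What the reply does not answer is that 80% power and 0.05 alpha are the stated basis for 5224 and for stopping there. They need zero between-period variation, which the protocol neither states nor justifies.

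**Conclusion.** The point holds in a limited form. The arithmetic behind 1306 is right for its formula, but the formula does not match assignment by period. The stated power and alpha are therefore conditional on an unstated assumption of no between-period variation. The fault lies in the power statement and in any inferential message-versus-control comparison made from pooled counts, not in the planned descriptive report by period.

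The size rests on assumed SDs of 1 to 2 points and an unknown number of passes. Across one to four passes, type I error of a pooled test would be about 6% to 24%, and correctly sized power with known variance about 76% down to 40%. Power falls further if the variance must be estimated from the three control periods of a single pass. The nested study's own claim should be corrected; the main trial result is untouched.

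**What to change.** 1. In the nested study's Sample Size paragraph, say that 80% power at 1306 per group assumes no variation in response between periods. State the planned number of passes, and give power over a range of assumed between-period SDs, computed for the analysis that will actually be used. The known-variance figures above should not be printed beside an analysis that estimates the variance.
2. In the Analysis paragraph, make the period the unit for any message-versus-control comparison. This can be done with period-level proportions, or with a binomial model with a random period effect or period-level overdispersion, using small-sample degrees of freedom. Weeks should not stand in for periods: weeks within one period share its deviation, so splitting does not recover period-level variance. If only one pass is run, present the comparison as descriptive and make no claim of 80% power.
3. Optional, if the distributor can switch advertisements more often: keep 5224 exposures but shorten the periods and repeat the sequence, so that each message appears in several periods.

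Items 1 and 2 cost wording and a somewhat more complex model, with no extra participants. The price is a less favourable power statement and wider intervals. Item 3 also needs more frequent switching by the distributor.
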